## 9. RESEARCH DESIGN AND METHODS

Research design: We will enroll an estimated 350 parent-child dyads to treat at least 160 parent-child dyads and randomize them into a 6 month, 20 session traditional FBT or FBT+PT. Families will be followed for 12 months post-treatment, making the total length of participation 18 months. Randomization will be conducted with a random number generator independent of the investigators. All children will be randomized by gender and randomization will be monitored throughout the proposal to determine whether any systematic differences in demography (age, race/ethnicity) or BMI% become evident. Treatment will take place at CHEAR in La Jolla or San Marcos, or remotely via password protected ZOOM meetings. Families randomized to FBT will take part in traditional 20-session group therapy for children and parents that includes nutrition/PA education as well as behavioral therapy components. Groups will include didactic sessions and problem solving. Families who are randomized to FBT+PT will participate in a 20 session program that focuses on teaching positive discipline strategies and effective parenting skills in addition to the components covered in traditional FBT. The process in these groups will include videotape modeling, role plays, and rehearsal (active skills training). Child groups will cover nutrition/PA information and basic behavioral strategies. Since the main difference between FBT+PT and FBT is the parenting training component, and it is not appropriate to introduce parenting issues to the children, the content of child groups will not differ between treatment arms. Once treatment is complete, families will be followed for one year post-randomization. Assessments will occur at baseline, post-treatment (6 months), and 6- and 12-months post-treatment/follow-up. Assessments will include height and weight data obtained during the study period, self-report measures, and videotaped family meals. All assessments that need to be conducted via virtual meetings will be conducted using password protected ZOOM meetings.

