### **Measures:**

Data from the child and the parent will be obtained specifically for research purposes. Data will be collected at 4 time points (baseline, post-treatment (6 months), and 6- and 12-months post-treatment). Assessments will be completed either in-person at the CHEAR office or in a password protected ZOOM meeting. The baseline assessment will include 3 approximately three-hour visits for the child and parent. At the baseline assessment, parents and children will complete surveys and be weighed and measured. Children will also wear an accelerometer for 7 days. Parents and children will be scheduled to complete a videotape family meal at their home. Following the first assessment visit, parents will be given the option of completing some surveys via the secure-web-based survey format prior to attending the in-person visit to reduce the amount of time they need to be present at CHEAR. If parents do not complete the surveys in advance, they will complete them as part of the visit. All surveys provided to be completed at home will include information that does not warrant immediate follow-up (i.e., no questions about suicidal ideation or self-harm). All surveys will be identified with the unique study ID rather than any identifying information. The assessments at follow-up time points (post-treatment (6 months), and 6- and 12-months post-treatment) will be similar to the baseline assessments and will consist of 2 approximately three-hour visits for the child and parent. In addition, families be offered the option of one additional assessment visit (similar to baseline) at post-treatment (6 months), and 6- and 12-months post-treatment, in order to evaluate the aims of the ancillary study. This visit will involve an additional consent form and additional compensation.

Weights will be obtained throughout the treatment program and heights will be obtained at the mid-treatment, post-treatment, and 6- and 12-months post-treatment assessment. The full battery of surveys, accelerometer data, dietary questions, and videotape assessment will occur again at post-treatment and 6- and 12-months post-treatment. A saliva sample for genetic material will only be obtained at baseline. A stool sample for microbiome analysis will be obtained at all time points. A full list of measures and assessments are listed in table 1.

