a) Anthropometry. Both child and parent will have their body size measured. Height will be measured using a portable Schorr height board in duplicate; body weight will be measured on a Tanita Digital

Scale (model WB-110A) in duplicate. The average of the two values will be used for analysis and will be translated for children to BMI for age percentile score using the CDC growth charts and to Body Mass Index (BMI) in parents ( $BMI=[kg/m^2]$ ). Children with a BMI  $\geq 85^{th}$  percentile and parents with a BMI  $\geq 25$  will be considered overweight.

- b) *Dietary intake.* Dietary intake of the child will be assessed with dietary knowledge questionnaire, which will assess eating habits of the children and the parents.
- c) *Physical activity.* Physical activity of the child and parent will be assessed using Actigraph accelerometers. Actigraph accelerometer (model GT1M, [www.theactigraph.com](http://www.theactigraph.com)) is a small (3.8 x 3.7 x 1.8 cm), lightweight (27 g), uni-axial accelerometer that is worn on a belt snugly around the waist. The GT1M records time varying accelerations ranging in magnitude from approximately .05 to 2 G's. We plan to ask participating children to wear the Actigraph for 7 consecutive days so that we may be able to assess within-person variation more precisely than if we collected data for only 4 days. Trained staff will instruct participating children and their parents on the proper procedure for attaching the Actigraph to their waistband and completing a log to record the times they did not wear the Actigraph (they'll be asked to remove the actigraph during sleeping time).
- d) *Sedentary behaviors & recreational media use.* Sedentary behaviors and media use will be assessed using an instrument developed in the PACE+ Adolescent trial. Both child and parent will complete this measure. This 8-item survey was based on a survey developed by Robinson and measures hours spent doing various sedentary behaviors during a typical school day and non school day. Analysis of the survey indicated that 3 factors account for 58% of the variance. The three factors were "Idle" (TV, computer/video games, listening to music, talking on the phone), "Intellectual" (homework, reading), and "Creative" (playing musical instrument, arts and crafts).

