## Analysis:

Analyses will be based on linear mixed models implemented in R statistical software and Mplus v 6.12. Primary outcomes evaluation first will follow an Intention to Treat principle with all missing values presumed returned to baseline level. Planned covariates for primary outcome, change in BMI z-score, will include gender, ethnicity, and parent marital status. For models evaluating the Primary Aim, fixed effects will include coefficients for time, treatment, and time by treatment interactions. For each outcome, selection of a covariance structure for the residuals will be based on fitting different structures (e.g., compound symmetry, unstructured) and selecting the one with the lowest sample size adjusted Akaike's Information Criterion. Significance tests will focus on the treatment by time interactions.

We will conduct analyses examining patient and therapist ratings of treatment acceptability and whether participants believe that the FBT+PT or FBT components address issues that are particularly relevant to them given the level of child behavioral problems. These analyses for the Secondary Aim will be conducted using regressions comparing FBT+PT to FBT. Survival analysis will assess the effect of FBT+PT on decreased risk for treatment drop-out (defined as subject refusal to continue treatment or failing to return to treatment without notification). Planned covariates in survival models will mirror primary analyses. Exploratory analyses will include use of generalized linear mixed effects models for repeated assessments of limited categorical and binary outcomes reflecting energy balance, video tape data, parenting, feeding/lifestyle behaviors, and psychosocial factors.

A multiple-mediator model will provide a test of whether FBT+PT leads to greater changes than FBT on proposed mediators ('a' paths) and whether changes in mediators (e.g., use of praise, limit-setting, problem-

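### The primary model for change in child BMI z-score does not adjust for baseline BMI z-score, which costs some precision and over-corrects chance baseline differences

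*Protocol*

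**What the plan says.** Protocol section 9, Analysis, sets out a linear mixed model for the primary aim. On covariates it says: "Planned covariates for primary outcome, change in BMI z-score, will include gender, ethnicity, and parent marital status". On structure it says: "fixed effects will include coefficients for time, treatment, and time by treatment interactions", and then: "Significance tests will focus on the treatment by time interactions". On missing data it says: "Primary outcomes evaluation first will follow an Intention to Treat principle with all missing values presumed returned to baseline level".

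The research design paragraph of section 9 randomises by gender and adds that "randomization will be monitored throughout the proposal to determine whether any systematic differences in demography (age, race/ethnicity) or BMI% become evident". Of the factors watched there, race/ethnicity has a counterpart in the covariate list. Age and BMI% do not.

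For the ancillary study, the exploratory analysis of change in the cognitive and reward measures does adjust for each measure's own baseline. The primary analysis has no such term. Child height and weight are measured at baseline (Table 1), so the value is available for every randomised child.

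**The concern.** There are two ways to read the model. Either baseline is one of the time levels of a repeated BMI z-score, or change from baseline is the response at each follow-up visit. In both, the comparison of arms at a visit is a difference in mean change. That uses baseline with a fixed coefficient of 1 instead of the coefficient the data support.

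Two things follow when the true coefficient is below 1. The comparison has a larger standard error than it need have. And if one arm starts heavier by chance, part of its later fall is regression to the mean, which the change score credits to the treatment. At stake is some power for the primary hypothesis and a result that depends more than necessary on the baseline draw.

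**Working it through.** **Inputs.** From the protocol: at least 160 randomised dyads, the covariate list, the model terms and the return-to-baseline rule. Assumed, because the protocol does not give them: the correlation r between baseline and follow-up BMI z-score (0.6 to 0.9), 1:1 allocation (80 per arm), and two-sided 5% for the power figures. The 160 is used only as a scale; the protocol states no target difference or power from which to reproduce it.

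**Step 1: what the tested contrast is.** After return-to-baseline imputation, the follow-up data are complete. In one simulated complete dataset (160 children, 4 visits, unstructured covariance), the treatment-by-time estimate at month 6 was -0.143232 (SE 0.032173). The raw difference in mean change was also -0.143232. So the model with free effects reproduces the change-score comparison.

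**Step 2: precision.** With equal SDs σ at both times, the variance per child is:

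- change score: 2σ²(1 - r)
- baseline-adjusted: σ²(1 - r²)
- ratio, adjusted to change: (1 - r²) / [2(1 - r)] = (1 + r)/2

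The equivalent number of extra children is 160 × [2/(1 + r) - 1]. The last column takes a change-score contrast with exactly 80% power and shows its power after adjustment.

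| r (assumed) | Variance cut | SE cut | Extra children at 160 | Power after adjustment |
|---|---|---|---|---|
| 0.9 | 5% | 2.5% | 8 | 82.0% |
| 0.8 | 10% | 5.1% | 18 | 84.0% |
| 0.7 | 15% | 7.8% | 28 | 86.0% |
| 0.6 | 20% | 10.6% | 40 | 87.9% |

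**Step 3: effect of return-to-baseline imputation.** Children set back to baseline have a change of zero, which weakens the link between baseline and change. In a simulation with 20% missing (the academic-setting drop-out quoted in section 7), with missingness unrelated to baseline, the variance ratio of change to adjusted was 1.039, 1.085, 1.134 and 1.184 for r = 0.9, 0.8, 0.7 and 0.6. The cut, 1 - 1/ratio, is then 3.8, 7.8, 11.8 and 15.5%. The worth at 160, 160 × (ratio - 1), is about 6, 14, 21 and 29 children.

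**Step 4: chance imbalance.** Let D be the baseline difference between arms and F the follow-up difference. The change score estimates F - D and the adjusted analysis F - rD, so they differ by (1 - r)D. If D equals one of its own standard errors, the gap in change-score SEs is (1 - r)/√[2(1 - r)] = √[(1 - r)/2]. That is 0.22 at r = 0.9, 0.32 at 0.8, 0.39 at 0.7 and 0.45 at 0.6. The gap favours whichever arm starts heavier.

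**Step 5: how far this depends on equal SDs.** If the follow-up SD is k times the baseline SD, the variance saved is σ²(1 - rk)², where rk is the slope of follow-up on baseline. The saving is never negative and is zero only when that slope is 1.

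**The case against.** The best defence is that baseline is not ignored. Change subtracts it, or it sits in the repeated outcome, so an imbalance is corrected, if imperfectly. That stands. A reader might infer that chance imbalance is left wholly uncorrected or that the estimate is biased; the documents support neither. The loss is in precision and in the estimate conditional on the baseline draw.

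The gain also rests on a correlation that the protocol does not give. At r of 0.8 to 0.9 it is only 2.5 to 5.1% of the standard error before imputation. That stands too, and sets the weight of the point. The wording of the list does not close it, and an analysis plan not seen here may add baseline. But the protocol has chosen three covariates, and baseline is the omission that is cheapest to repair.

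Four stronger readings are tempting and should not be drawn.

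- **Child age and site.** "Treatment will take place at CHEAR in La Jolla or San Marcos, or remotely via password protected ZOOM meetings" may suggest adjusting for site or delivery mode. If baseline is a time level and the data are complete, main effects of age and site leave treatment-by-time unchanged: in the simulated dataset, estimates and SEs agreed to six decimals. Entered with time interactions, they gave no gain there (month-6 SE 0.032615 against 0.032173). BMI is already referenced to age, and site is not a stated stratification factor.
- **Delivery mode.** It is a sound covariate only if fixed before randomisation, which the protocol does not say.
- **Measurement mode.** The protocol says "Assessments will be completed either in-person at the CHEAR office or in a password protected ZOOM meeting" and also "Height will be measured using a portable Schorr height board in duplicate". How remote heights are obtained is a separate question, and any assumed error has no source in the text. Mode at each visit arises after randomisation and may relate to arm or engagement, so conditioning on it could introduce bias.
- **Interference with allocation.** Monitoring of balance might be read as an invitation to intervene. The protocol keeps the random number generator separate from the investigators and describes no action on allocation.

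**Conclusion.** The point holds as a modest efficiency improvement to the primary model. Leaving out baseline BMI z-score gives up about 5 to 20% of the variance of the arm comparison for assumed correlations of 0.9 down to 0.6, or about 4 to 16% with 20% of children returned to baseline. It also lets a one-SE baseline difference move the estimate by 0.22 to 0.45 SE. These figures rest on the assumed correlations, equal SDs, 1:1 allocation and, for the imputed case, missingness unrelated to baseline. The direction does not rest on the particular correlation: adjustment loses nothing beyond a few degrees of freedom and gains unless the slope of follow-up on baseline is 1. The point does not extend to bias on average, to other covariates or to the conduct of randomisation.

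**What to change.** In section 9, Analysis, state whether baseline BMI z-score is a response row or change from baseline is the response, and name the contrast at each visit that is then the treatment effect. After that:

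- if change is modelled, add baseline BMI z-score and its interaction with visit as prespecified covariates;
- if baseline is a response row, do not also enter it as a covariate, but constrain the two arms' baseline means to be equal.

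Keep the three named covariates if they are wanted, but note that as main effects in a complete response-row model they do not alter treatment-by-time when the arms' baseline means are left free. The cost is a sentence of protocol text and a few degrees of freedom. No new data are needed, since baseline height and weight are already collected.

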**6. SPECIFIC AIMS**

Authoritative parenting style has been associated with decreased obesity risk in children and can modify the delivery and impact of weight control strategies, making them more effective. At this time, gold-standard treatment for childhood obesity is family-based behavioral therapy (FBT). This treatment relies on behavioral strategies and the use of praise and a positive reinforcement system to change eating and activity behaviors, but does not target other aspects of parenting. Broadening parenting instruction to include effective limit-setting behaviors, parent-child communication, and authoritative parenting may increase parents' confidence and ability to successfully make behavior changes and modify the impact of the behavioral strategies being used.

In this application, we propose to test the efficacy of a 6 month, 20-sessions, weight control program that combines traditional family-based behavioral therapy with comprehensive parenting training (FBT+PT) and compare it to traditional family-based behavioral therapy (FBT). The FBT+PT arm will incorporate more active

skills learning to increase adoption of authoritative parenting behaviors. We will recruit and randomize 160 overweight/obese children (BMI>85th percentile and <99.9th percentile) between 7 and 12 years old and their parent into a 6 month, 20-sessions FBT+PT or FBT program and follow them for 1 year post-treatment. The primary outcome is change in child body weight (BMI z-score). Our secondary aim will be to evaluate the effect of both treatments on drop-out rates, adherence, and acceptability. As an exploratory aim, we will evaluate parent and child level mediators and moderators of weight loss in each of the treatment arms in order to inform future treatment development. We will achieve the goals of this application by pursuing the following primary and secondary aims:

- **Primary aim 1:** Examine the efficacy of FBT+PT on child body weight compared to gold standard FBT. *We hypothesize that FBT+PT will show greater decreases in child body weight (BMI z-score) compared to FBT at post-treatment and 6- and 12-months post-treatment.*
- **Secondary aim 1:** Examine drop-out, treatment adherence, and acceptability in FBT+PT and FBT. We hypothesize that families randomized to FBT+PT will have lower drop-out rates, increased program adherence (including attendance, self-monitoring, use of praise), and higher ratings of acceptability.

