Treatment elements: Both treatment arms will consist of 20 weekly group meetings for parents and children. Parent group meetings will last 90 minutes each week and discuss principles of behavior change, nutrition and physical activity. Children will also meet in a separate group at the same time and discuss nutrition and physical activity topics that correspond to the parent meetings. Both parents and children will receive weekly manuals and activities to do at home. The purpose of the manual is to provide key components of family-based behavioral treatment to the families and reinforce what is being taught in groups. Child manuals will provide similar content as the parent manual but be developmentally appropriate for children age 7-12 years old. Parents will also be asked to meet daily with their child to discuss/monitor eating and activity behaviors and other aspects of the program. Parents will be expected to report back on their experiences the following week.

Additional parenting strategies will be addressed in FBT+PT and active skills training used to reinforce these behaviors and parenting style. The parenting training component will be adapted from The Incredible Years Program (IYP). This program is based on social learning models of parent-child interaction and encourage parents to use emotionally supportive behavior and assertive discipline techniques (rather than coercive or negative reinforcement techniques) when interacting with and educating their children. Parents learn how to *use positive reinforcement strategies, use more effective discipline strategies, improve communication techniques, learn how to monitor child behaviors, regulate their own emotions, and problem solve*. This program uses active skills training (e.g. *video modeling, role play and behavioral practice in class, group discussions and problem-solving, and emotion regulation training*) to increase skills adoption. Using these techniques, parents can observe others interacting with children in ways that promote positive behaviors

and can practice “doing it right”. This method allows parents to gain greater insight into the impact of their behaviors, receive immediate feedback, has been shown to be effective at producing behavioral changes, and is not currently used in traditional FBT.

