During the first half of each session in FBT+PT, group leaders will address basic behavioral, nutrition, and PA information similar to what is addressed in FBT. Parenting strategies will be introduced and practiced during the second half of the session. Two-minute parenting skills vignettes that demonstrate positive and negative parent-child interactions will be shown by group leaders and discussed with parents. These vignettes have been developed by IYP and are available for purchase. Vignettes that model parents interacting with their child in food and PA situations will be emphasized. After viewing each vignette, parents will discuss what they have seen and practice the targeted skills, receiving feedback from group leaders and other parents. All parents will be expected to role-play during group to help increase mastery of the parenting skills. Parents will problem solve with the group while also learning how to self-manage their thoughts, emotions, and behaviors. Group leaders will reiterate the principle parenting technique that is being addressed and discuss how to use these techniques in different family situations to help increase generalization of the behavior. After each session, parents will also be given assignments to practice these skills at home. At the end of these types of programs, parents often feel more competent to engage in these newly practiced parenting behaviors and learn how to self-monitor their emotions and behaviors, cope with challenges, and seek appropriate support when needed. This more interactive format has been successful at decreasing the use of harsh discipline and critical statements and increasing supportive parenting, displays of affection, and praise.

*Quality Control for Treatment:* Close monitoring through multiple methods will be used to ensure treatment integrity. Interventionists (FBT+PT, FBT) will attend full day trainings with Drs. [name], [name] and [name]. All interventionists will meet weekly with a licensed clinical psychologist in separate supervisions. Intervention sessions will be audiotaped for ongoing performance monitoring. Random samples (e.g., 20% or more) of all intervention sessions will be rated for fidelity by an independent rater using a measure created for this study. Tapes will be destroyed within three years of completion of the study.

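### The primary model as written ignores correlation within therapy groups; if change in BMI z-score is correlated within groups, the standard errors of the treatment-by-time contrasts are too small

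*Protocol*

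**What the plan says.** Three parts of Protocol Section 9 matter here.

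- **Allocation.** The unit is the child with a parent: "All children will be randomized by gender". Section 6 gives the number: "We will recruit and randomize 160 overweight/obese children".
- **Delivery.** "Both treatment arms will consist of 20 weekly group meetings for parents and children". This covers the control arm too: "Families randomized to FBT will take part in traditional 20-session group therapy for children and parents". In FBT+PT, influence between families is part of the method. After each vignette "parents will discuss what they have seen and practice the targeted skills, receiving feedback from group leaders and other parents".
- **Analysis.** The primary analysis uses linear mixed models: "For models evaluating the Primary Aim, fixed effects will include coefficients for time, treatment, and time by treatment interactions". The covariates are gender, ethnicity and parent marital status. The residual covariance is chosen among structures such as compound symmetry and unstructured by "selecting the one with the lowest sample size adjusted Akaike's Information Criterion". Testing centres on treatment by time, and the first analysis sets missing values back to baseline.

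No term, robust variance or design effect for therapy group, cohort or leader appears anywhere in the protocol. The drop-out survival model takes the same covariates as the primary model, and the acceptability comparison is a regression between arms. Neither has a group term.

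**The concern.** Families who share leaders, discussion and weekly meetings for 20 sessions may end up with more similar outcomes than families in different groups. Each group belongs to one arm, so any group-level variation in change adds to the variance of the arm difference. The residual structures that the protocol names describe correlation between visits of one child. None of them describes correlation between children. Under the written model, 160 families count as 160 independent observations of change.

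At stake is the reliability of the p-value and confidence interval for the single primary aim. The same gap exists in the drop-out and acceptability analyses, although its size there was not calculated.

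**Working it through.** **Stated figure.** There is none to reproduce. The protocol gives 160 children but no significance level, power, standard deviation, group size, number of groups or ICC.

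**Inputs.** N = 160 comes from Section 6. The following are assumptions: 1:1 allocation (80 per arm), equal groups of m = 8 (10 groups per arm) or m = 10 (8 groups per arm), a two-sided 5% test, and an ICC from 0 to 0.10. The relevant ICC is that of *change* in BMI z-score, because the treatment-by-time contrast at a given visit is a difference between arms in mean change from baseline.

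**Formulas.**
- Design effect: DE = 1 + (m − 1) × ICC
- True SE divided by model SE: √DE
- Actual error: 2 × [1 − Φ(1.960/√DE)]
- Effective N: 160/DE

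**Example, ICC 0.05.**
- m = 8: DE = 1 + 7 × 0.05 = 1.35; √DE = 1.162; 1.960/1.162 = 1.687; error 9.2%; effective N = 160/1.35 = 118.5.
- m = 10: DE = 1 + 9 × 0.05 = 1.45; √DE = 1.204; 1.960/1.204 = 1.628; error 10.4%; effective N = 160/1.45 = 110.3.

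**Full range (m = 8 / m = 10).**

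| ICC | DE | SE ratio | Actual error | Effective N |
|---|---|---|---|---|
| 0 | 1.00 / 1.00 | 1.00 / 1.00 | 5.0% / 5.0% | 160 / 160 |
| 0.01 | 1.07 / 1.09 | 1.03 / 1.04 | 5.8% / 6.0% | 149.5 / 146.8 |
| 0.02 | 1.14 / 1.18 | 1.07 / 1.09 | 6.6% / 7.1% | 140.4 / 135.6 |
| 0.05 | 1.35 / 1.45 | 1.16 / 1.20 | 9.2% / 10.4% | 118.5 / 110.3 |
| 0.10 | 1.70 / 1.90 | 1.30 / 1.38 | 13.3% / 15.5% | 94.1 / 84.2 |

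**Simulation check** (20,000 trials per setting, 80 per arm, one change score per child). Ignoring groups at ICC 0.05 gave 9.3% (m = 8) and 10.7% (m = 10). A t-test on group means gave 4.9% to 5.2% at every ICC from 0 to 0.10.

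**Does a plain group intercept repair it?** No. Write the outcome of child i in group g at visit t as fixed effects + u(g) + child effect + residual. The contrast for visit t is the arm difference in (visit t − baseline). The term u(g) appears in both visits and subtracts out, so with every visit filled the estimate and its model-based standard error are unchanged whatever variance u(g) is given. Filling missing values with baseline produces exactly this balanced layout. A simulation agrees (400 trials per setting, 20 groups of 8, four visits, group effect arising after baseline). For the month-18 contrast, rejection was 10.0% without and 10.0% with the group intercept at ICC 0.05, and 13.0% and 13.0% at ICC 0.10. The group term must therefore be allowed to differ between baseline and later visits.

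**The case against.** The strongest objection is that the omission is inferred from silence. The sentence on the primary model lists fixed effects only. A linear mixed model may contain random effects that are not listed, and a statistical analysis plan that is not at hand could supply them. This is fair as far as that one sentence goes. But the Analysis section sets out the fixed effects, covariates and residual covariance together, and the ancillary part of the same section does name its random intercepts. So it is right to say that the model as written does not account for group. It would go too far to say that the final analysis cannot.

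The second objection is that the size is assumed. This stands. The loss is nil at ICC 0 and about one percentage point at ICC 0.01, and the error roughly doubles only near ICC 0.05.

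A reader might draw three stronger conclusions that the documents do not support:
- **That the false-positive rate certainly exceeds 5%.** This needs a positive ICC, a group size and a significance level, and the protocol gives none of them.
- **That group or leader differences bias the treatment estimate.** The point here is understated variance. If leaders differed systematically by arm, a random group effect would not remove that, and the protocol does not say how leaders are assigned.
- **That groups have fixed membership and that membership is already on file.** The protocol says neither.

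**Conclusion.** The point holds in conditional form. The design creates a level of dependence, the therapy group, that the written primary model leaves out. If change in BMI z-score is positively correlated within groups, the treatment-by-time standard errors are too small: by 3-4% of their stated size at ICC 0.01, 16-20% at 0.05 and 30-38% at 0.10, for 8 to 10 families per group.

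These figures rest on equal groups, 1:1 allocation and a contrast at one visit. A joint test over all visits, and the effect of baseline filling on the ICC, were not modelled. For drop-out and acceptability the same omission is present, but no size is claimed.

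**What to change.** Amend the Analysis part of Section 9 as follows.

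1. Record the therapy group of each family as a data item.
2. Add to the primary model a random therapy-group effect that acts on change. This can be a group-by-time random effect, or a group random effect in a baseline-adjusted or change-score model at each visit. State that a group intercept constant over visits does not serve this purpose.
3. Use Kenward-Roger or Satterthwaite degrees of freedom, because the number of groups is small.
4. Use a matching frailty term in the drop-out model and a group-level random effect in the acceptability models.

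Only the analysis wording and one recorded variable change. The cost is somewhat wider intervals and fewer degrees of freedom. With 20 groups a group-level comparison has 20 − 2 = 18 degrees of freedom and a critical value of 2.10. With 16 groups it has 16 − 2 = 14 and 2.14. Against 1.96, intervals would be about 7% to 9% wider from this source alone (2.101/1.960 = 1.07; 2.145/1.960 = 1.09), even if the ICC turned out to be zero.
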